### **DATA SOURCE**

The data for the Semi-Annual Reports will be drawn from existing electronic medical records at each City AIDS Center. The Electronic HIV Case Management System (EHCMS) is a government-approved computer system for the collection, storage, transfer and analysis of epidemiological, laboratory and clinical data on all registered cases of HIV infection in Kazakhstan. Within this system, a file is created for each client who registers for treatment at the AIDS Center. All visits, tests, results and treatment information for each client are regularly entered by staff from the epidemiology and treatment department. . This system has been in place since 2011, and is used in all regions of the country. Each AIDS Center is responsible for assuring the quality of entered data through regular checks by specialists.

### **REPORT LOGISTICS**

#### *Regions*

Data will be collected from city AIDS Centers in the four study sites: Almaty, Shymkent, Karaganda, and Temirtau.

#### *Frequency*

As this report draws data from the AIDS Centers' existing medical records, there is no need for additional data collection outside the AIDS Centers' usual scope of work. The reports will be prepared for GHRCCA every six months over the period from November 2016 to May 2020.

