### *2.2 STUDY DESIGN*

Bridge will be implemented in four cities, in Kazakhstan: Almaty, Shymkent, Temirtau & Karaganda. Due to their geographical proximity of Temirtau and Karaganda, and overlapping administration of HIV clinics they will be considered as one “site” for intervention roll out. In month 16, we will use computer software to sequentially randomly assign the three sites six months prior to implementing BRIDGE in months 22, 28 and 34.

We opted for a stepped wedge trial over a cluster RCT for ethical reasons so that all clusters will eventually receive the intervention as well as to avoid contamination and to be able to control for exogenous time specific effects as discussed earlier. The unit under experimental control will be a city, with the timing of roll-out of BRIDGE in each of the study’s cities—Almaty, Shymkent Karaganda, and Temirtau—to be randomly assigned. Since the cities are geographically disparate (with the exception of Karaganda and Temirtau, which is why we will consider them as a single study site) the likelihood of participant contamination is minimal.

The stepped wedge approach represents a scientific alternative to the randomized control trial (RCT) by providing a valid counterfactual to evaluate the impact of BRIDGE compared to the TP Standard of Care. This roll out design also more closely resembles the method of implementing BRIDGE in a real-world setting. The use of multiple groups and our data analytic plan will allow us to control for exogenous time-specific effects, such as introducing new HIV initiatives or funding cuts and minimizes contamination as all TP sites in a city will receive BRIDGE at the same time. More importantly, this design addresses important ethical considerations of communities by ensuring that all TP sites will eventually receive BRIDGE, which is a potentially lifesaving intervention.

The following figure describes the stepped-wedge rollout of Bridge in the four cities (with Karaganda & Temirtau combined as one study site):

Figure 2: Stepped Wedge Design

[figure not shown]

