Analysis of Program data: Formal hypothesis testing based on program data will test for differences in outcome measures obtained during the pre-intervention period (i.e., time points before BRIDGE is implemented in a city) versus periods when BRIDGE is implemented. We will employ permutation tests (a.k.a. “randomization tests”) for significance testing because of concerns that the distribution of measures may not be approximated well by a small sample size (i.e.,  $N=24$  TPs). In experimentally controlled trials with small sample sizes, permutation tests have been shown to be superior to parametric tests. As a heuristic and non-parametric approach, permutation testing more accurately estimates the nominal type I error rate for cluster randomized clinical trials with small sample sizes and with measures that may not be normally distributed compared to candidate parametric procedures. Strong hypothesis testing in this manner involves permuting the BRIDGE implementation status of each time point; since the time period “assignment” (pre-implementation vs. BRIDGE) is allocated based on city, permutations will account for clustering by city (i.e., a permutation for TPs in the same city will all be assigned the same implementation status for that time point). Not only does this conservatively account for shared variance that might be present due to being located in the same city, statistical efficiency can be improved by clustered permutation testing. For inference, the test statistic (difference in means) observed based on actual period assignments is compared vis-à-vis the distribution of test statistics using permuted assignments, with the proportion of permuted test statistics greater than the actual observed taken as the one-sided or half of the two-sided p-value. With program measures collected quarterly over 42 months, the number of clustered permutations with 3 study sites (4 cities) is 38,416, allowing testing of statistical significance with  $\alpha < .0001$ . If we permute all 24 TPs independently, tests of significance can be performed with much lower  $\alpha$ . We will conduct both permutation tests with sites permuted independently as well as clustered permutations by city and report the result with the more conservative p-value. Hypothesis testing for Aims 1 and 2—i.e., estimating the effectiveness of the intervention—will involve

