### Post-Implementation Survey

Following the start of the intervention in each city, the nurse will administer a post-implementation survey on an electronic tablet to every client who comes to the trust point or AIDS Center. The Post-Implementation survey will contain questions regarding which services were administered to the client, including, in the Trust Point Nurse surveys, the BRIDGE intervention components of SNS recruitment (whether the client was referred as part of the peer recruitment strategy) and ARTAS (whether the client completed an ARTAS session during that visit). No personally identifiable information will be collected. Responses will be linked to a unique study ID number for each client. The Post-Implementation Survey will take approximately 5 minutes to complete.

Study sites will switch from the pre-implementation to the post-implementation survey once BRIDGE is rolled out in their city. Due to the stepped-wedge design of BRIDGE, each study site will make this switch at a different time. A graphic is provided below, where month 13 (the start of data collection) is November 2016.

[figure not shown]

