## INDICATORS PROVIDED IN REPORT

Semi-annual reports shall contain following indicators:

- BRIDGE ID (as index)
- Age
- Sex
- Date when client's HIV-positive status was confirmed
- Name of the trust point where client has received services in the past 6 months
- Date registered as client of the AIDS Center
- Was the client given a CD4 test in the past 6 months?
  - Test system used for CD4
  - Results of CD4 test
- Was the client given a Viral Load test in the past 6 months?
  - Test system used for Viral Load
  - Results of Viral Load test
- Clinical Stage of Disease in the past 6 months
- Has the client begun ART?
  - Date when the client begun ART
  - Name of ART drugs (regimens)
- Changes in the client's ART regime in the past 6 months
- Changes in the specific ART medications in the past 6 months
- Testing for STIs at the AIDS Center in the past 6 months
  - STIs diagnosis in the past 6 months (if available)
  - Treatment for STIs (if available)
- Registration at the drug treatment clinic

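### Each rollout falls inside a six-month AIDS Center report window whose viral load and CD4 items are undated, and the report lacks fields for retention and adherence

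*Combined protocol and SAP*

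**What the plan says.** **Calendar.** Appendix A (Post-Implementation Survey) states that "month 13 (the start of data collection) is November 2016". Section 2.2 plans random ordering of three sites, "implementing BRIDGE in months 22, 28 and 34". Appendix B (Frequency) says: "The reports will be prepared for GHRCCA every six months over the period from November 2016 to May 2020". The program data follow a finer grid (Section 2.4): "With program measures collected quarterly over 42 months".

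**Report content.** In Appendix B (Indicators Provided in Report), CD4 and viral load are each a six-month look-back question plus a result, for example "Was the client given a Viral Load test in the past 6 months". No test date is listed. Dates are listed for HIV confirmation, AIDS Center registration and ART start. No visit count, visit date or adherence item appears.

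**What the report is for.** Appendix B (Purpose of Report) assigns it retention, ART initiation, adherence and viral suppression, and plans to compare BRIDGE with non-BRIDGE trust points. Table 1 defines retention as at least three HIV clinic visits in 90 days, with two sources: this report and AppSheet.

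**Analysis.** Section 2.4 uses a permutation test on the difference in means between pre-implementation and BRIDGE periods. It bases power for Aims 1 and 2 on viral suppression, as the smallest effect, and reports 80% power with 24 trust points. No passage says how to code a report window that contains a rollout.

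**The concern.** A stepped-wedge comparison takes its information from the periods in which some sites have crossed over and others have not. Here those are the three windows that contain a rollout, and in each of them one site is part exposed. For an item known only as having occurred within six months, such a window cannot be divided. Coding it as pre or as post misclassifies part of it and pulls the estimate towards zero. The outcome exposed to this is viral suppression, on which the power statement rests.

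Separately, two outcomes assigned to the report (retention and adherence) need fields that its template does not contain.

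**Working it through.** **1. Reproduce the stated span.** November 2016 to May 2020 is (2020×12+5) − (2016×12+11) = 24,245 − 24,203 = 42 months, which agrees with Section 2.4. That is 42/6 = 7 report windows or 42/3 = 14 quarters.

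**2. Place the rollouts.** Assume windows start in November and May and that rollout is at the start of the stated month.

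| Rollout | Date | Window | Exposed share |
|---|---|---|---|
| Month 22 | Aug 2017 | months 19-24 | 3/6 |
| Month 28 | Feb 2018 | months 25-30 | 3/6 |
| Month 34 | Aug 2018 | months 31-36 | 3/6 |

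So 3 of 3×7 = 21 site-windows straddle a rollout, one per site.

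**3. Difference in means.** Take a unit effect, immediate and constant, with equal weight per site-window. Let f be the exposed share of a straddling window. There are 5+4+3 = 12 fully exposed cells, 3 straddling and 6 unexposed.
- Coded post: share kept = (12+3f)/15. At f = 0.5 this is 13.5/15 = 0.90.
- Coded pre: share kept = 1 − 3f/9. At f = 0.5 this is 0.83.

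**4. Site- and period-adjusted model.** Regress true exposure E on coded exposure T with site and window effects. Share kept = S(TE)/S(TT), where S is the sum of products after removing site and window means. Coded post, f = 0.5:
- S(TT) = 15 − 11 − 13.667 + 10.714 = 1.048
- S(TE) = 13.5 − 9.929 − 12.667 + 9.643 = 0.548
- Share kept = 0.548/1.048 = 0.52

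For general f the share is 1/22 + (21/22)f coded post and 1 − (21/22)f coded pre.

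**5. Sensitivity.**

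| Case | f | Means, post | Means, pre | Adjusted, post | Adjusted, pre |
|---|---|---|---|---|---|
| Cut-off one month earlier | 1/3 | 0.87 | 0.89 | 0.36 | 0.68 |
| November/May cut-off | 1/2 | 0.90 | 0.83 | 0.52 | 0.52 |
| Cut-off one month later | 2/3 | 0.93 | 0.78 | 0.68 | 0.36 |
| November/May, effect delayed 3 months | 0 | 0.80 | 1.00 | 0.05 | 1.00 |

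If the November 2016 report is itself a look-back, making eight windows, the adjusted figure at f = 1/2 is 0.54.

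**6. Alternatives.** On quarters (13-15, 16-18, 19-21, 22-24 and so on) months 22, 28 and 34 each open a quarter, so 0 of 3×14 = 42 site-quarters straddle and the share kept is 1.00. On six-month windows, omitting the straddling cells or entering f as exposure also keeps 1.00. In the adjusted model, with independent cells of equal variance, the estimator's variance is then 2.44 (omitted) or 1.83 (fractional), against 0.95 for the biased coding, in units of residual variance.

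**7. Fields against outcomes.**

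| Outcome assigned to the report | Field needed | Listed? |
|---|---|---|
| ART initiation | start date | yes |
| Viral suppression | result and test date | result only |
| Retention | visit counts or dates | no |
| Adherence | an adherence measure | no |

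The source system does hold visits (Appendix B, Data Source): "All visits, tests, results and treatment information for each client are regularly entered by staff".

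**The case against.** **Other outcomes have dated data.** A reader might infer that all Aim 2 effects are diluted by up to half. The documents do not support that. ART start is dated in the report. Retention and HIV testing can come from AppSheet, which is completed at trust point and AIDS Center visits and is date-stamped. The primary outcome also comes from AppSheet on the quarterly grid. This objection stands and confines the dilution to the undated items, viral load and CD4.

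**Retention has a second source.** A reader might also infer that 90-day retention cannot be computed at all. It can, for enrolled clients of BRIDGE trust points. But AppSheet IDs are issued only at those trust points (Appendix A, ID Numbers). The report uses a separate ID whose key stays at the AIDS Center, and no link between the two is described. The comparison with non-BRIDGE trust points therefore still lacks visit data.

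**AppSheet may record viral load testing.** The consent description includes viral load and CD4 among tests received. The survey forms are not available here, so whether results are captured is unknown. Appendix A assigns AppSheet only testing and retention under Aim 2.

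**The largest dilution depends on an unspecified model.** The stated statistic is a difference in means, where the loss is 10% to 17%. The mixed-model and GEE text covers the primary aim and names no period terms. This stands. The adjusted figure is still relevant because Section 2.2 justifies the design by its control of time-specific effects.

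**Coding, cut-offs and effect shape are assumed.** This is fair. No passage fixes the coding or the extraction dates, and viral suppression probably lags rollout. A three-month delay would make coding the window as pre correct and coding it as post worse. That is a reason to state the rule in advance.

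**Conclusion.** The point holds for viral suppression (and CD4), for the retention comparison between BRIDGE and non-BRIDGE trust points, and for adherence. Within 0.36 to 0.68, the adjusted share depends on cut-off and coding; at the assumed cut-off the loss is about 48% adjusted and 10% to 17% in the difference in means. These sizes assume one value per site per report window, rollout at the start of the month, equal weights, and an immediate, constant effect. That the windows straddle the rollouts is firmer: moving the cut-off a month either way leaves exposure at 1/3 or 2/3. The effect on the stated 80% power cannot be derived, because its effect size and intraclass correlation are in a figure that is not shown.

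Aim 2 is secondary and the loss can be repaired, so this is a correction to make rather than a threat to the primary result.

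**What to change.** 1. Add to the Appendix B indicator list the date of each viral load and CD4 test and of each AIDS Center visit, or else quarterly visit counts and test results, drawn from the electronic case management system.
2. Analyse report outcomes on the quarterly grid already used for program data.
3. State in advance that, for any report delivered without dates, the crossover window is omitted or entered as fractional exposure, and accept the larger variance.
4. Remove adherence from the outcomes assigned to this report, or name the field that measures it.

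The cost is slightly more extraction work. Staff and the six-monthly delivery schedule do not change.

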#### *Staff*

We will hire two staff members from each City AIDS Center to prepare these reports. These staff will be currently employed members of the AIDS Center staff who already have access to the EHCMS as part of their job:

1. Data manager - specialist from epidemiological department with access to personal data of HIV positive clients and data from national electronic tracking system for HIV cases.
2. Administrative staff member – will ensure data collection, preparation of semi-annual reports and quality assurance at the AC for GHRCCA.

### **DE-IDENTIFICATION OF PATIENT DATA**

Data provided to GHRCCA staff will be stripped of all PII identifiers. As they are preparing the report each period, AIDS Center staff will substitute patient name with a randomly assigned BRIDGE ID (a simple four digit index number). The AIDS Center personnel responsible for report preparation will keep the only copy of the list that links the patient's name with his/her BRIDGE ID on an encrypted endpoint device. BRIDGE and GHRCCA staff will not have access to this list.

## INDICATORS PROVIDED IN REPORT

Semi-annual reports shall contain following indicators:

- BRIDGE ID (as index)
- Age
- Sex
- Date when client's HIV-positive status was confirmed
- Name of the trust point where client has received services in the past 6 months
- Date registered as client of the AIDS Center
- Was the client given a CD4 test in the past 6 months?
  - Test system used for CD4
  - Results of CD4 test
- Was the client given a Viral Load test in the past 6 months?
  - Test system used for Viral Load
  - Results of Viral Load test
- Clinical Stage of Disease in the past 6 months
- Has the client begun ART?
  - Date when the client begun ART
  - Name of ART drugs (regimens)
- Changes in the client's ART regime in the past 6 months
- Changes in the specific ART medications in the past 6 months
- Testing for STIs at the AIDS Center in the past 6 months
  - STIs diagnosis in the past 6 months (if available)
  - Treatment for STIs (if available)
- Registration at the drug treatment clinic

## DATA MANAGEMENT & SECURITY

### Data Management Systems to Preserve Confidentiality

The data provided in these reports are highly sensitive, and a number of steps are taken to ensure complete confidentiality and compliance with HIPAA regulations regarding the use of medical data.

The EHCMS is a secure, computer-based system certified by the Kazakhstan Ministry of Health as a repository for sensitive health information. The system has been in use since 2011, and has the following security features: 1) access is limited only to a limited number of epidemiology department and treatment department staff; 2) the system is password protected; 3) the system is stored on encrypted endpoint devices (AIDS Center computers); 4) AIDS Center IT staff are responsible for regular security checks and protections for these devices.

Record extraction from this database is done by those who already have access to it: the epidemiological staff at each City AIDS Center.

The de-identification process, likewise, is put under the control of staff who are already authorized to access PII about each client. Each AIDS Center PWID client will be assigned a random 4-digit number (we suggest a 1001, 1002, 1003, etc. formula); the list linking client name to BRIDGE ID number will be stored in an electronic format on an AIDS Center computer. These computers are encrypted and password protected, and the epidemiologist hired to prepare the report is the only one who will have access to this list.

De-identified data will be entered into the report, which is in an Excel format. The file will be password protected. To transfer the data to the BRIDGE research team every six months, the AIDS Center will be provided with an encrypted hard drive. BRIDGE staff will receive this hard drive in-person from the AIDS Center. These study procedures ensure minimum risk of the loss of confidentiality around this data.

## Data Analysis Plan for Primary Study Aim

### Hypothesis:

Compared to pre-implementation time blocks, time blocks where Bridge is implemented will have increased numbers of PWID clients who (a) attend NSPs, (b) receive a rapid test for HIV at NSPs, and (c) link to HIV care at the AIDS center, when their test is positive for HIV care in the past 6 months)

### Formal hypothesis testing:

Hypothesis testing draws on data from the Google app-based data collection system. The primary test for these hypotheses will be based on patient visits to NSPs, compared at the site (NSP) level. This test will utilize a repeated measures approach and will examine differences in outcome measures obtained during the time points before Bridge is implemented in a city (pre-implementation) versus time points that follow the initiation of Bridge intervention implementation (implementation) in the city. We will employ permutation tests (a.k.a. “randomization tests”) for significance testing because of concerns that the distribution of measures may not be approximated well by a small sample size (e.g.,  $N = 24$  NSPs). Hypothesis testing in this manner involves permuting the Bridge implementation status of each time point; since the time period “assignment” (pre-implementation vs. Bridge intervention implementation) is allocated based on city, permutations will account for clustering by city (i.e., a permutation for NSPs in the same city will all be assigned the same implementation status for that time point). Not only does this conservatively account for shared variance that might be present due to being located in the same city, statistical efficiency can be improved by clustered permutation testing. For inference, the test statistic (difference in means) observed based on actual period assignments is compared vis-à-vis the distribution of test statistics using permuted assignments, with the proportion of permuted test

statistics greater than the actual observed taken as the one-sided or half of the two-sided p value.

This data requires an analytic approach that accommodates for the non-independence in measures arising from two sources: (1) correlations due to repeated measures with the same NSP and (2) correlations due to NSPs operating in the same city. Hypothesis testing will rely on Generalized Linear Mixed Models (GLMM) and Generalized Estimating Equations (GEE) as recommended for stepped-wedge trials. GLMM is exceedingly flexible and powerful but may not be robust to violations of normality assumptions, which will be examined using various descriptive statistics and further can exhibit difficulties in convergence in some cases. GEE is more robust; however, GEE assumes that missing data are missing completely at random while GLMM assumes that data are missing at random. The exact choice will be informed by the results from analyses that shed insight into the extent that various assumptions hold or are violated (e.g., attrition analyses, parameterization fits). In either case, sandwich estimators for variance will be used which are robust to misspecification of the correlation structure. We will use a link function that can properly model the outcome variable as a function of measurement unit or distribution (e.g., logit for binary outcomes, Poisson or Negative Binomial for count and/or rare outcomes).

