examination of the population-level effect in the statistical models to make inferences about the treatment effect.

Power analyses for Aims 1 and 2: Estimates of power to detect significant differences for each hypothesis was conducted. Power analyses were conducted using G\*Power (v3.1.0), two-tailed hypothesis testing, and  $\alpha=.05$ ; results are presented separately for site level data (Figure 3). For site level data, the smallest effect size for Aims 1 and 2 proportion achieving undetectable viral load; power analyses for this “rate limiting” effect size used unconditional exact test to simulate permutation testing method of estimating p-values as well as simulated cluster permutation (i.e., TPs in a city covary together). The autocorrelation and clustering effects were modeled as overall “intraclass correlation” (ICC), using a range of ICCs observed in our prior studies. Results indicate 80% power is achieved with a sample size of 24 TPs (Figure 4).

[figure not shown]

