separate protocol, in the peer recruiter consent form, and in the peer recruiter brief survey. Peer recruiters and clients will be apprised during informed consent that the BRIDGE Program is being run at trust points as part of a research study conducted by CU and GHRCCA (and that all program materials have received approval from the CU IRB). An electronic data system designed by the project will be used to track the number of returned coupons, recruitment links, and non-client referrals using the coupon management system. Senior TP outreach workers will identify the first set of peer recruiters, through internal TP participation or referral from TP clients or other agencies. Senior TP outreach workers will train peer recruiters to identify, screen, and invite other PWID in their social networks to participate in CTR services and become peer recruiters. Senior TP outreach workers will continue to engage peer recruiters and provide ongoing coaching and support about how they can approach and effectively engage their injecting network associates using culturally tailored messages that are designed for PWID who never initiated care, dropped out of care or were not considered for ART because their CD4 count was >350. Network associates who accept CTR services will be escorted to the TP, a nurse will provide CTR at the TP and then the network associate will be engaged as a potential recruiter for SNS.

The BRIDGE intervention manual describes the SNS recruitment strategy component of the intervention, where social networks are used to bring PWID into the trust points for testing. After this initial recruitment, it is the responsibility of the trust point nurse/social worker to engage clients in rapid testing and ARTAS, as set forth in the intervention manual. All PWID who receive rapid HIV testing under the BRIDGE intervention or participate in ARTAS case management sessions will undergo an informed consent procedure to acknowledge that de-identified data on services received will be provided to the BRIDGE study. This informed consent is described in more detail below. Clients of the trust point have the right to refuse to participate in all or individual BRIDGE activities.

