#### 5. STUDY SUBJECTS

According to the Republican AIDS Center, there were an estimated total of 25,394 PWID in the 4 cities with an average of 597 registered PWID clients per TP in 2014. The 24 TP study sites should yield a pool of potential 14,328 PWID participants of whom it is estimated 13.3% on average will test positive for HIV ( $n=1,891$ ) based on RAC surveillance reports of HIV prevalence rates in the 4 cities. This existing pool of potential TP registered clients in addition to new PWID clients recruited during the two year enrollment period should be adequate to assess

program outcomes for Aim 1 and Aim 2 outcomes.

*Gender and Minority Inclusion:* We anticipate that 80% of the PWID and TP staff and nurses will identify as Asian, 30% of PWID will be women, and 50% of the TP staff and HIV Care Center nurses will be women.

*Participation of Children:* The study will include women and men aged 18 or over, including youth 18 to 20 years of age. Younger children will be excluded because the BRIDGE intervention has not been designed for them and they are not currently served by TP. The investigative team includes certified social workers who are trained to work with young adults aged 18 to 20 years.

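### ART initiation and viral suppression are analysed with an on/off rollout status and no role for time since rollout, so a delayed benefit could be understated or, in a period-adjusted model, read as null or harmful

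*Combined protocol and SAP*

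**What the plan says.** Protocol section 2.4 (Analysis of Program data), which covers Aims 1 and 2, compares "time points before BRIDGE is implemented in a city) versus periods when BRIDGE is implemented". The Data Analysis Plan for Primary Study Aim repeats this coding: the second arm of the contrast is "time points that follow the initiation of Bridge intervention implementation (implementation) in the city". In both places the statistic is "the test statistic (difference in means) observed based on actual period assignments", referred to a permutation distribution. The data analysis plan then adds GLMM or GEE, naming two sources of correlation (repeated measures within a trust point, and trust points within a city) but no calendar-period term. Section 2.2 says that the design and analysis will control for time-specific outside influences.

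Section 2.2 sets the schedule: "implementing BRIDGE in months 22, 28 and 34". Appendix A places the start of data collection at month 13 (November 2016). Appendix B has the AIDS Center reports prepared every six months from November 2016 to May 2020. They cover all HIV-positive PWID served by the center, and many items look back six months. Appendix B names ART initiation and virologic suppression among the outcomes tested from these reports.

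On recruitment, section 3.3 describes a chain: after testing, "then the network associate will be engaged as a potential recruiter for SNS". Section 5 mentions "new PWID clients recruited during the two year enrollment period".

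The power paragraph in section 2.4 reports 80% power with 24 trust points and rests on "the smallest effect size for Aims 1 and 2 proportion achieving undetectable viral load". The only run-in found in the text is staff training one month before rollout (sections 4 and 9).

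**The concern.** Suppression is the last link of a sequence: a peer recruits, the client is tested, attends ARTAS, registers at the AIDS Center, starts ART, and later has a viral load measured. BRIDGE cannot move it on the day of rollout. It is also measured among all HIV-positive PWID at the center, including people whom BRIDGE has not reached. The analysis nevertheless scores the first post-rollout period exactly like one two years later.

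Two things are at stake. The written contrast averages early periods with little possible effect into the intervention mean, which shrinks the estimate. Second, once a calendar-period term is present, early sites that are already on BRIDGE serve as comparators for later ones. All sites are on BRIDGE from month 34 and the steps are six months apart, so a delayed effect is partly subtracted from itself. An effective program could then be reported as having no effect, or an adverse one, on suppression.

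**Working it through.** **The plan's own figure.** The 80% cannot be reproduced. The readable text prints no effect size, baseline rate or ICC, and the power figure is not shown.

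**Schedule.** Quarterly measures over 42 months give 42/3 = 14 quarters, months 13 to 55. Pre-rollout quarters are (22-13)/3 = 3, (28-13)/3 = 5 and (34-13)/3 = 7. Post-rollout quarters are 11, 9 and 7, in total 27.

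**Assumptions.** No document gives a lag, so it is shown as a range. The effect is zero until the lag has passed and 1 afterwards, and there is no secular trend.

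**Difference in means, as written.** Each quarter of lag removes one effective quarter at each of the three sites, so the retained fraction is f = (27 - 3k)/27 for k quarters of lag.

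**Single step term with site and period effects.** Least squares on the 3 x 14 grid: outcome = site + quarter + b x (0/1 status). The coefficient b is the retained fraction.

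| Assumed lag | Difference in means | Step term with period effects |
|---|---|---|
| 0 | 27/27 = 1.00 | 1.00 |
| 3 months | 24/27 = 0.89 | 0.52 |
| 6 months | 21/27 = 0.78 | 0.05 |
| 12 months | 15/27 = 0.56 | -0.27 |

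**The six-monthly grid.** Suppression is reported every six months, so the quarterly grid is finer than its data. If reports close at months 19, 25, 31, 37, 43, 49 and 55, there are 7 reports x 3 sites = 21 cells. The first report after each rollout covers months 19-25, 25-31 and 31-37. Rollout falls at 22, 28 and 34, so each of these reports contains 22-19 = 28-25 = 34-31 = 3 pre-rollout months, yet is scored as implemented. Post-rollout reports number 6 + 5 + 4 = 15. A lag of one report leaves 12/15 = 0.80 in the difference in means and 0.05 in the step term; a lag of two leaves 9/15 = 0.60 and -0.27. The coarser grid does not change the picture.

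**Power, conditionally.** Suppose the 80% refers to a full effect from the first day. Then power = Phi(f x (1.96 + 0.84) - 1.96), which gives 70%, 59% and 34% for f = 0.89, 0.78 and 0.56. If the planned effect is already an average over post-rollout periods, f = 1 and power stays at 80%. The text does not say which applies.

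**Precision of an exposure-time model.** On 21 cells, take 3 site terms, 6 period terms and an indicator for every report since rollout. There are 6 such indicators if the straddling report counts as post-rollout (15 parameters, 6 residual df), and 5 if it counts as pre-rollout (14 parameters, 7 residual df). From the diagonal of (X'X)^-1, the standard error of the first-12-month average is about 1.4 and 1.2 residual SD respectively, against 0.98 for the step term.

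**The case against.** The strongest reply has four parts.

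- **Power.** A reader might infer that the stated 80% is not delivered. The documents do not support that: the effect size is unreadable and may already be a post-rollout average. This objection stands in full.
- **Primary outcomes.** The data analysis plan tests whether more clients "a) attend NSPs, (b) receive a rapid test for HIV at NSPs, and (c) link to HIV care at the AIDS center". Attendance and testing are counts per time block that can rise as soon as recruitment begins, so a reader who infers that the primary analysis is biased goes beyond the text. This also stands. Linkage is less clear, since it carries a look-back of 90 days in Table 1 and six months in the hypothesis; that justifies a sensitivity analysis, not a charge of bias.
- **The two-year period.** A reader might take it as a 24-month uptake curve at each site. Section 5 uses it to describe the size of the client pool for the study as a whole; it gives no site-level curve and no shape. The size therefore rests on assumed lags only.
- **The period term.** The near-zero and negative values need a calendar-period term, which the data analysis plan does not write. For the written difference in means the result is attenuation, never a change of sign. That is correct as far as it goes. But section 2.2 promises control of time effects, and a GLMM or GEE needs such a term to keep that promise.

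The figures that are not shown might display a transition period. Its absence is a reading of the text alone.

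**Conclusion.** The concern holds for ART initiation and viral suppression. Every post-rollout period is scored as fully implemented, although the documents describe outcomes that must follow rollout with a delay and reports that straddle it. For assumed lags of 3 to 12 months, the written contrast keeps 0.89 to 0.56 of the full effect. A period-adjusted single-step model keeps 0.52 to -0.27, so a real but delayed benefit could be reported as null or harmful. These fractions rest on the assumed lag, on a sharp onset and on the stated schedule; they do not depend on the unreadable effect size or ICC. The effect on the 80% power is undetermined. No bias is shown for attendance or testing. This is a change worth making before analysis, not a reason to discard the planned test.

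**What to change.** - **Keep the planned analysis.** For ART initiation and viral suppression, pre-specify in section 2.4 and the data analysis plan a supplementary model with site, calendar-period and time-since-rollout terms on the six-monthly grid. For example, use 0-6, 6-12 and over 12 months since rollout, with the straddling report as a transition period.
- **Report the effect by exposure time.** A first-12-month average alone would not serve. On the quarterly grid it is 2/4 = 0.50 at a 6-month lag and 0/4 = 0.00 at 12 months, below the 0.78 and 0.56 of the planned contrast.
- **Interpretation rule.** Do not interpret a null or negative single-step estimate without the exposure-time results.
- **Linkage.** Run the same model as a sensitivity analysis.
- **Power paragraph.** State whether the effect behind the 80% is a full-exposure effect or a post-rollout average. If it is a full-exposure effect, restate power under a stated uptake lag.

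The cost is wording and one extra model, with no new data. The downside is precision: in the version with an indicator for every report, the standard error of the 12-month average is 1.2-1.4 residual SD against 0.98, with 6-7 residual df. With three sites, and none untreated after month 34, late exposure effects also lean on the assumption that sites share one exposure curve. The model should therefore be labelled supportive, not a replacement.
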